## Abstract

**Background:**

People with mild cognitive impairment (MCI) are at increased risk of converting to dementia. Cognitive training can improve the cognitive abilities of people with MCI. Computerised cognitive training (CCT) offers several advantages over traditional paper-and-pencil cognitive training and has the potential to be more individualised by matching task difficulty with individual performance. Recent systematic reviews have reported promising effects of CCT on improving the cognitive capacities of people with MCI. However, the quality of existing studies has been limited, and it is still unclear whether CCT can influence the progression to dementia. We developed an ‘individualised’ CCT (MAKSCog) specialised for people with MCI that automatically matches task difficulty with individual performance and an active control training (‘basic’ CCT). The aims of the present study are (a) to evaluate MAKSCog and (b) to investigate whether it can be applied to maintain the cognitive abilities of people with MCI.

**Methods:**

The present study investigates the effects of CCT on cognition in a randomised controlled intervention study in Germany. Participants are community-dwelling people with a psychometric diagnosis of MCI based on the Montreal Cognitive Assessment (MoCA) and Mini-Mental Status Test (MMSE). Screening and baseline testing are conducted via a videoconferencing assessment and telephone. Participants are randomly allocated. The treatment phase is 6 months with an open phase in which participants can freely decide to continue to use the CCTs. Additionally, both CCTs contain a monthly computerised cognitive assessment that measures different cognitive abilities: information processing speed, memory span, short term memory, and logical reasoning.

**Discussion:**

This is the first study to investigate the effect of MAKSCog, an individualised CCT, specifically developed for people with different subtypes of MCI. A methodological strength is the double-blind, randomised, controlled design and the use of basic CCT as an active control group. The study is conducted entirely virtually with valid telehealth assessments for cognitive function. Methodological limitations might include a restriction to participants who feel comfortable with the use of technology and who own a computer, laptop, or tablet.

**Trial registration:**

ISRCTN ISRCTN14437015. Prospectively registered on 27 February 2020.

## Introduction

Dementia is a challenging disease for healthcare systems around the world [1]. The term mild cognitive impairment (MCI) has been created to describe a transitional state between normal ageing and the early onset of Alzheimer’s disease (AD) [2]. It refers to a state that is defined by the presence of early cognitive impairments that do not yet constitute a dementia syndrome and only very slightly impaired instrumental activities of daily living [3–5]. People with MCI may remain stable, revert back to normal cognition, or progress to dementia [6]. About 15% of people with amnestic MCI in which memory dysfunction is most prominent will progress to having AD annually [7]. In non-amnestic MCI, the impairment of other cognitive features such as language, visuospatial, or executive functions predominates. In the general population, the prevalence of MCI increases with age, at 6.7% for ages 60 to 64 and up to 25.2% for ages 80 to 84 [6].

MCI is the optimal period for intervention so that conversion to AD can be prevented. Pharmacological treatments are not convincing [6], leaving non-pharmacological interventions as the only feasible approach to preventing AD. The available research has focused primarily on physical exercise and cognitive training as the two most significant protective factors for dementia [6, 8]. Still, further research is needed. Cheng et al. [8] concluded that physical exercise and cognitive training might support cognitive functioning in different ways: physical exercise training as ‘hardware’, thus preserving neuronal structural integrity and brain volume, while cognitive training works as ‘software’, thus strengthening the functioning and plasticity of neural circuits.

Cognitive training, traditionally presented as a paper-and-pen exercise, has found its way into the digital world in the form of computer-based tasks that include cognitive exercises, games, and virtual reality. Its emerged popularity can be ascribed to safety, low implementation costs, high availability, and accessibility. Yet another advantage is the potential to provide real-time feedback and more individualised training to participants by adapting task difficulty to individual performance [9]. There is even evidence that computerised training is an effective alternative to paper and pencil cognitive training with comparable or better effect sizes in cognitively healthy community-dwelling older adults [10].

A considerable amount of research evaluating the effects of computerised cognitive training (CCT) for people with MCI has emerged during the last decade (for an overview, see, e.g. [11]). The field is growing rapidly. Previous systematic reviews and meta-analyses of CCT intervention studies have demonstrated promising effects on improving the cognitive capacity of people with MCI [11–16]. For example, across 17 randomised controlled trials (RCT) of moderate quality, Hill et al. [12] reported an overall moderate effect size for cognition (Hedges’ *g* = 0.35) and concluded that CCT is a useful intervention for enhancing cognition in people with MCI. More recently, Zhang et al. [11] reported a small positive effect size for global cognitive function (Hedges’ *g* = 0.23) and moderate positive effect sizes for memory (Hedges’ *g* = 0.30) and working memory (Hedges’ *g* = 0.39). Benefits to mood (depression, anxiety, and apathy) were reported in a meta-analysis that also investigated outcomes in everyday life of cognitive interventions, including CCT in people with MCI [15]. In a recent Cochrane review including eight RCTs, Gates et al. [17] evaluated the effects of at least 12 weeks of CCT on maintaining or improving cognitive functioning and preventing dementia in people with MCI. They applied rigorous quality assessments of the studies. Only very cautiously, they concluded that people with MCI might benefit from CCT in terms of improved cognitive function. Limitations were the very low quality of the evidence and an unclear or high risk of bias in several domains in most of the studies, especially the blinding of participants and personnel. Across all trials, data on incident dementia was missing, which was also claimed by Zhang et al. [11]. Irazoki et al. [18] evaluated 19 studies and provided a qualitative synthesis of the features of different computerised cognitive programs. All of the eleven tools they reviewed had multiple target groups, and there were only two that were specifically marked for people with MCI as the target group.

We developed an easy-to-use software application (MAKSCog for maximum cognition) specifically designed for people with MCI that is available for computer, laptop and tablet and can be used from home. The basis for the development was the non-pharmacological multicomponent MAKS® intervention [19], which has been shown to be an effective treatment for people with MCI and mild and moderate dementia in two independent RCTs [20–22]. The cognitive component of MAKS® was the basis for the development of MAKSCog. What makes MAKSCog special is that the application contains a learning system that automatically chooses exercises that match the person’s level of difficulty, thus allowing for more individualised training. MAKSCog was developed for all subtypes of MCI and addresses different cognitive functions.

The aims of the present study are (a) to evaluate MAKSCog, an individualised CCT for people with MCI and (b) to investigate whether it can be applied to maintain the cognitive abilities of people with MCI. We are comparing MAKSCog with a basic CCT that primarily focuses on leisure activities and serves as an active control condition.

The objective of this paper is to describe the study protocol of our RCT while following the evidence-based reporting guidelines of the SPIRIT Statement [23].

## Methods and analyses

### Objectives

#### Research hypothesis

Individualised CCT (MAKSCog) will lead to statistically significantly greater improvements in cognitive capacities over time in people with MCI as compared with basic CCT (active control group).

#### Exploratory study question

In an open phase of the study, we will investigate long-term cognitive status yearly.

### Study design and setting

A prospective double-blind randomised controlled intervention study is being conducted to test the abovementioned research hypothesis. The overall start date of the study was on 01 April 2019. Recruitment began on 16 March 2020 and will continue until 31 January 2021. The study is being carried out in the metropolitan region of Erlangen/Nürnberg, Bavaria, Germany. At baseline, all study participants are randomly assigned to the intervention (individualised CCT; MAKSCog) or active control group (basic CCT). The reasons for choosing an active control group are as follows: First, since the principal usefulness of CCT is well known [11–16], it would be unethical to use a control group without CCT. Second, by using an active control group, we will be able to evaluate the additional effect of the learning system. After baseline testing (t0), the study participants receive one of the two computerised training applications for their computer, laptop or tablet. It is recommended that they use the training at least 30 min per day 3 days a week during the 6-month intervention phase. Both computerised training applications contain the same computerised cognition assessment that will be delivered and collected once a month (t0–t6). After the end of the 6-month intervention phase, the study participants in both the intervention and control groups will be free to decide whether or not to continue using the computerised training. Then the open phase of the study will begin in which we will examine the exploratory study question. Trial registration data are presented in Table 1.

**Table 1 Tab1:** Trial registration data

Data category	Information
1. Primary registry and trial identification number	ISRCTN14437015
2. Date of registration in primary registry	27.02.2020
3. Secondary identifying numbers	-
4. Source(s) of monetary or material support	Reinhard Frank-Stiftung
5. Primary sponsor	Reinhard Frank-Stiftung
6. Secondary sponsor(s)	-
7. Contact for public queries	see point 8
8. Contact for scientific queries	[name]. [name], [contact]
9. Public title	Dementia prevention for older people suffering from mild cognitive impairment using computerised cognitive training tools
10. Scientific title	Individualised computerised cognitive training for community-dwelling people with mild cognitive impairment
11. Countries of recruitment	Germany
12. Health condition(s) or problem(s) studied	Mild cognitive impairment (MCI)
13. Intervention(s)	Intervention group: Individualised computerised cognitive training, which involves targeted exercises for memory span, information processing, visual-spatial cognition, etc.
	Control group: basic computerised cognitive training, which involves basic exercises for memory span, information processing, visual-spatial cognition, etc.
14. Key inclusion and exclusion criteria	Inclusion criteria: 1. MCI 1.1. Montreal Cognitive Assessment score (MoCA) ≤ 24 1.2. Mini Mental State Examination score (MMSE) ≥ 24 2. Own computer/laptop/tablet and basic skills in their use3. Age ≥ 60 4. Informed consent given
	Exclusion criteria: 1. Completely blind or deaf 2. No personal computer, laptop, or tablet 3. Normal cognition, MoCA ≥ 24 4. Dementia, Mini-Mental Status Examination score < 24 5. Depression, Patient Health Questionnaire 9 score (PHQ-9) ≥ 12 6. Apparent neurological diseases and/or other severe psychiatric diseases
15. Study type	Prospective double-blind randomised controlled intervention study
16. Date of first enrolment	09.06.2020
17. Target sample size	-
18. Recruitment status	incomplete
19. Primary outcome(s)	Cognition measured by the Montreal Cognitive Assessment (MoCA) at baseline and after 6 months
20. Key secondary outcomes	Cognition measured by reaction time and logical thinking assessments delivered and collected by the digital software at baseline and after 1, 2, 3, 4, 5 and 6 months, Mini-Mental Status Examination (MMSE) at baseline and after 6 months Exploratory outcome measures: Long-term cognitive status assessed using the Montreal Cognitive Assessment (MoCA) and the Mini-Mental Status Examination (MMSE), yearly in the open phase

Data are being collected by means of psychometric tests and structured interviews using videoconferencing and telephone. The data ​are being collected by trained student assistants who have no knowledge of group allocation at any time. The procedure is as follows. One of the researchers prepares a folder with the installation application for each study participant on which the software for the assigned computerised training version is located. Shortly before baseline testing (t0), the study participants receive an email with a link to download the software for their version of the computerised application and instructions on how to download and install the software. The participants are not told which of the two applications they are using. At follow-up (t6), after the assessment has been completed, each study participant will also receive an application-specific questionnaire about the usability of the software.

### Sample size and effect size estimation

A power analysis was computed with 100 study participants who were distributed to the two groups of the 2x2 factorial variance-analytic experimental design with one repeated measurement (factor 1: two CCTs; factor 2: two time points). With 50 study participants in each group, alpha = 0.05, beta = 0.20 (corresponding to a power of 80%), a correlation between repeated measures of 0.5 and a nonsphericity correction of 1, we will have the power to detect effects with an effect size of *f* ≥ 0.14 (comparable to Cohen’s *d* ≥ 0.28).

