### Data collection

The data are being collected at baseline (t0) and at the end of the 6-month intervention period (t6). As the span between screening and t0 is approximately 2 weeks, we use the MoCA and MMSE of the screening as baseline values. For the exploratory study question, the data are being collected on a yearly basis after the baseline assessment with no specified end point (see Fig. 1). Due to the COVID-19 pandemic, we decided to eliminate the risk of infection related to study participation. The trial will be conducted entirely virtually. All data will be generated via videoconferencing, telephone, or the computerised cognitive assessment that is integrated into the CCTs. The participants were instructed in an invitation mail or letter to prepare an undisturbed environment for the videoconferences. However, participants lacking the hardware for a videoconference or those who are not willing to take part in an assessment by videoconference will be given the option to come into the clinical research centre for their screening visit or follow-up. Testing with the MoCA and MMSE will be conducted via videoconferencing with the student assistants. Videoconferencing assessments with the MoCA and MMSE have very high reliability scores compared with face-to-face testing. The intraclass correlation coefficients (ICC) for the MoCA and the MMSE have been demonstrated in several studies and go up to ICC = 0.99 for the MoCA [47] and up to ICC = 0.92 for the MMSE [48]. The questionnaire on sociodemographic and health-related data will be sent to the study participants to prepare them for the telephone interview. The data collected by the computerised cognitive assessment during the 6-month intervention period will be obtained from the study participants.

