### Data analysis

All relevant data, sociodemographic, health-related, primary, and secondary outcome variables will be reported descriptively. In order to be able to assess the quality of the randomisation, the baseline data from the intervention and control groups will be tested for statistically significant differences. For the multivariate analyses, we will impute missing values using the expectation maximum algorithm. The primary hypothesis will be tested by calculating multivariate analyses according to the general linear model. To ensure the robustness of the results, we will perform both analysis strategies ‘intention to treat’ and ‘per protocol’. ‘Intention to treat’ evaluations are carried out with all cases still alive at the end of the intervention or observation period. The significance level is defined as alpha = 0.05. The data analyses will be performed using the ‘IBM SPSS Statistics 24’ software. The members of the data monitoring committee are [name]. [name] and one of his statistics experts from the Institute of Medical Informatics, Biometry, and Epidemiology, Friedrich-Alexander Universität Erlangen-Nürnberg, [name].

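### The implied primary test is a comparison of MoCA change scores. It is valid, but adjusting t6 MoCA for screening MoCA and sex would be at least as precise at almost no cost.

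*Protocol article*

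**What the plan says.** All references are to the protocol article.

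- **Sample size and effect size estimation.** The calculation is for a "2x2 factorial variance-analytic experimental design with one repeated measurement (factor 1: two CCTs; factor 2: two time points", with 50 participants per group, alpha 0.05, 80% power and "a correlation between repeated measures of 0.5 and a nonsphericity correction of 1". The result is a detectable f of 0.14.
- **Research hypothesis.** MAKSCog is expected to give "greater improvements in cognitive capacities over time in people with MCI as compared with basic CCT (active control group".
- **Data analysis.** The primary hypothesis is to be tested with multivariate analyses under the general linear model. Neither the interaction nor a baseline covariate is named. The same section says that "the baseline data from the intervention and control groups will be tested for statistically significant differences", in order to judge the quality of the randomisation.
- **Data collection.** "we use the MoCA and MMSE of the screening as baseline values". Under Eligibility of participants, a MoCA of 24 or less is required for entry, so the baseline of the primary outcome is also the score that selected the sample.
- **Randomisation.** Allocation is stratified by sex.
- **Introduction, aim (b).** The study also asks whether MAKSCog can be applied to preserve cognition in people with MCI.

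**The concern.** With one baseline and one follow-up, the group-by-time interaction of a 2×2 mixed ANOVA is the two-sample t-test on change. Subtracting the baseline fixes its slope at 1. When the correlation between the two measurements is well below 1, the best slope is smaller, and the subtraction adds noise that regression on baseline would avoid. The trial has 100 participants and already holds the screening MoCA, so any precision lost this way could be had for free.

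There are two matters of interpretation as well. Participants are selected on a low MoCA and that same value serves as baseline, so both arms are expected to score higher at t6 even if neither program works. A repeated-measures ANOVA reports a time main effect that would pick up this rise, and aim (b) invites a within-arm reading. Secondly, significance tests on baseline variables cannot show whether randomisation was sound: if it was, every difference is due to chance.

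**Working it through.** **1. Which test was powered.** Inputs from the sample size section: N = 100, m = 2 time points, ρ = 0.5, ε = 1, α = 0.05, f = 0.14.
- Within-between interaction: λ = f²·N·m/(1−ρ) = 0.0196 × 100 × 2/0.5 = 7.84 on F(1, 98). Power is 79.2%, and 80% is reached at f = 0.1415. The stated figure reproduces.
- Between-group main effect: λ = f²·N·m/(1+ρ). Power at f = 0.14 is 36.0%, and the detectable f is 0.245. This does not match.
- Interaction with α = 0.10 (the one-sided equivalent): detectable f = 0.125. This does not match.

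The time main effect has the same formula as the interaction, but the hypothesis is comparative, so the interaction is the test implied. For this interaction the between-arm difference in change is 4f = 0.56 outcome SD.

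**2. Change score against ANCOVA with equal SDs.** Variance per participant in units of the outcome variance (equal SDs are my assumption; the article does not state them):
- Change: 2(1−ρ) = 1.00
- ANCOVA: 1−ρ² = 0.75
- Ratio: (1+ρ)/2 = 0.75, a 25% reduction

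| 50 per arm, ρ = 0.5 | Change (df 98) | ANCOVA (df 97) |
|---|---|---|
| Detectable difference, 80% power | 0.566 SD | 0.490 SD |
| Power at 0.56 SD | 79.2% | 89.3% |
| n per arm for 80% power at 0.56 SD (normal approximation) | 51 | 38 |

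Adding sex (df 96) leaves the 89.3% unchanged. For an assumed ρ of 0.3 to 0.8 the variance reduction runs from 35% to 10%.

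**3. The same comparison with a truncated baseline.** Let r be the correlation in the unselected population and v the variance of the truncated baseline relative to the untruncated variance. The change variance is (1−r)²·v + (1−r²), and the ANCOVA variance is 1−r².
- Cut at the population mean (assumed): v = 1−2/π = 0.363. For r = 0.5 the ratio is 0.75/(0.25 × 0.363 + 0.75) = 0.75/0.841 = 0.89. For r = 0.7 it is 0.51/(0.09 × 0.363 + 0.51) = 0.51/0.543 = 0.94.
- In simulation (10,000 trials per scenario) with r = 0.5, the SE fell from 0.183 to 0.174, about 10% in variance, and power at 0.56 SD rose from 86% to 89%. With r = 0.7 the variance gain was about 5%.
- Cut at 24.5 with an assumed screened-population mean of 25–26, SD 2.5–3.5 and r of 0.6–0.85: ratios 0.92 to 0.98, a gain of about 2–8%.

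**4. Regression to the mean.** The expected rise in each arm without any effect is (1−r)(μ − E[X | X ≤ 24.5]). Under the assumed ranges just given, this is 0.35 to 1.52 MoCA points. In the simulation with r = 0.5 and the cut at the mean, both arms rose by 0.40 SD under no effect. The between-arm difference averaged 0.00 and type I error was 5.1% for both methods. With a true effect of 0.56, both methods estimated 0.56.

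**5. Baseline tests.** If 25 independent variables were tested (an assumed count), the chance of at least one p < 0.05 under perfect randomisation is 1 − 0.95²⁵ = 0.72.

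**The case against.** **The interaction is never named as the primary test.** This stands. It is inferred from the hypothesis and the power calculation, and ANCOVA is itself a general linear model, so the data analysis section does not exclude it. Covariates are often left to a SAP, which is not at hand. The request is therefore to name the model, not to replace a test declared wrong.

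**The 25% gain and the truncated baseline pull against each other.** This also stands. The 25% needs equal SDs, and truncation at 24 makes the baseline SD smaller. The modest gain is the more realistic one.

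**A reader might infer that using the selecting score as baseline biases the treatment comparison, or that ANCOVA removes regression to the mean.** The documents support neither. Selection comes before randomisation, so the rise is equal in expectation in both arms and cancels in the contrast. ANCOVA does not remove it from within-arm change; it only adjusts for chance baseline imbalance. No passage plans a test of within-arm change. The opening for a misreading is aim (b), together with the time main effect that the powered model reports.

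**The baseline tests do no harm to inference.** This is true as written, since the plan does not use them to choose covariates or alter the primary analysis. The 72% also overstates precision, because items such as income and education are not independent. What remains is that the stated purpose of these tests cannot be met.

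**Conclusion.** The concern holds as one of efficiency and wording, not of validity. The implied change-score test keeps its type I error and is unbiased. ANCOVA was at least as precise in every scenario computed. The gain is a 25% variance reduction (power 79% to 89% at 0.56 SD) at the protocol's correlation if SDs are equal at both times. It is probably about 2–10% once the baseline is truncated, a range that rests on assumed population means, SDs and retest correlations that the article does not give. Regression to the mean leaves the between-arm contrast untouched but will make both arms look improved, so within-arm change must not be read as benefit. The baseline significance tests are a correct but minor point.

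**What to change.** 1. In the data analysis section, name the primary analysis as ANCOVA of t6 MoCA on arm, screening MoCA and sex (the stratification factor), fixed before the data are examined. The cost is one or two degrees of freedom and no new data.
2. Add a sentence that only the adjusted between-arm contrast tests the hypothesis, and that within-arm change and the time main effect are not evidence of benefit or, for aim (b), of preserved cognition.
3. Describe baseline balance by arm with summary statistics or standardised differences, and drop the significance tests.

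All three are changes of wording. The sample size can stay as it is; any precision gained is a margin.

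### The detectable effect is converted wrongly: f = 0.14 for the group-by-time interaction is a difference in change of about 0.57 SD, not d = 0.28, where power is about 28%

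*Protocol article*

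**What the plan says.** The section on sample size and effect size estimation describes a "2x2 factorial variance-analytic experimental design with one repeated measurement (factor 1: two CCTs; factor 2: two time points"). The stated inputs are "With 50 study participants in each group", alpha 0.05, "beta = 0.20 (corresponding to a power of 80"%), a correlation of 0.5 between the repeated measures and a nonsphericity correction of 1. The result is given as "the power to detect effects with an effect size of *f* ≥ 0.14 (comparable to Cohen’s *d* ≥ 0.28"). The section does not say which difference d refers to.

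The research hypothesis sets the contrast of interest: MAKSCog is expected to produce "greater improvements in cognitive capacities over time in people with MCI as compared with basic CCT (active control group"). That is a between-group difference in change. The primary outcome is the MoCA at baseline and 6 months (Table 1, item 19).

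**The concern.** The two effect sizes in the power statement differ by a factor of exactly two (0.28 = 2 × 0.14). That is the conversion for comparing two independent means. It does not carry over to the interaction in a 2x2 repeated-measures design, and the interaction is what the hypothesis tests.

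Most readers will look at d, because it is the figure they can set beside other trials. The Introduction cites pooled effects of g = 0.23 for global cognition, 0.30 for memory, 0.35 for cognition overall and 0.39 for working memory. A trial said to detect d ≥ 0.28 appears able to find effects of that order. If the true threshold is twice as large, a non-significant result could be taken as evidence against effects of about 0.3 SD that the trial had little chance of detecting. The comparator is itself a computerised training, chosen so that the added effect of the learning system can be evaluated, so a large contrast cannot be taken for granted.

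**Working it through.** **Inputs.** N = 100 (50 per group), m = 2 time points, correlation ρ = 0.5, nonsphericity correction ε = 1 and power 80%, all from the sample size section. The Data analysis section confirms the alpha: "The significance level is defined as alpha = 0.05". Sidedness is not stated; the F test with 1 numerator degree of freedom corresponds to a two-sided t test. Below, σ is the SD of the outcome at a single time point and δ is the between-group difference in change.

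**Step 1: reproduce f.** For the group-by-time interaction, λ = f²·N·m·ε/(1 − ρ), with 1 and 98 degrees of freedom.

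- At f = 0.14: λ = 0.0196 × 100 × 2 / 0.5 = 7.84, power 79.2%.
- Power of exactly 80% needs f = 0.1415.

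The protocol's f ≥ 0.14 is therefore reproduced. For comparison, the between-subjects main effect at f = 0.14 has only 36% power, and a one-way comparison of two means 28%. The stated f is the interaction f.

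**Step 2: convert f to a difference in change.** Let both groups start at 0, with the control group staying at 0 and the MAKSCog group reaching δ at month 6. With δ = 0.56σ:

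- grand mean 0.14, group means 0.28 and 0, time means 0 and 0.28;
- interaction effect in the MAKSCog month-6 cell: 0.56 − 0.28 − 0.28 + 0.14 = 0.14.

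All four cells have interaction effects of ±0.14σ. In general they are ±δ/4, so f = δ/(4σ) and δ = 4fσ. Hence f = 0.14 is δ = 0.56σ, and f = 0.1415 is δ = 0.566σ.

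**Step 3: check with a t test on change scores.** The SD of change is σ·√(2(1 − ρ)) = σ·√1 = σ. The noncentrality is (δ/σ)·√(50/2) = 5δ/σ.

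| True difference in change (SD) | Noncentrality | Power, 50 per group |
|---|---|---|
| 0.23 | 1.15 | 21% |
| 0.28 | 1.40 | 28% |
| 0.30 | 1.50 | 32% |
| 0.35 | 1.75 | 41% |
| 0.39 | 1.95 | 49% |
| 0.56 | 2.80 | 79.2% |
| 0.566 | 2.83 | 80% |

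The 79.2% at 0.56 equals the F-test result in Step 1 (2.80² = 7.84). A simulation of 10,000 trials gave 28.8% at 0.28 and 77.9% at 0.56.

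**Step 4: sample size for d = 0.28.** About 201 per group (normal approximation; 202 with the t distribution), roughly four times the 50 planned, as expected when the target effect is halved.

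**Step 5: does another reading give 80% at 0.28?**

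- Baseline-adjusted ANCOVA, ρ = 0.5: residual SD σ·√(1 − 0.25) = 0.866σ. Power at 0.28 is 36%; 80% is reached at 0.49.
- One-sided alpha 0.05: 40% at 0.28.
- Higher correlation, change scores: 43% at ρ = 0.7 and 59% at ρ = 0.8; 80% needs ρ of about 0.88.
- Pre-post change in all 100 participants pooled: 79.2% at 0.28, but this does not compare the groups.
- A month-6 group difference of 0.28σ gives interaction f = 0.14 only if the groups differ by 0.28σ in the opposite direction at baseline, which randomisation rules out in expectation.

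**The case against.** The strongest reply is that the power analysis itself is correct. The 80% is attached to f, which reproduces, and only the bracketed gloss is faulty. The gloss is worded loosely, d is never defined, and doubling f is the usual conversion between the two measures. It is true that the error lies only in the conversion. But d tells the reader what difference the trial can detect, the only between-group contrast in the hypothesis is the difference in change, and loose wording does not cover a factor of two.

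A second reply is that 0.57 is not the only possible answer, because the Data analysis section names only a general linear model. That is fair: the figure belongs to the repeated-measures analysis that was powered. Baseline adjustment would lower it to 0.49, still far above 0.28.

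Third, the sample size section does not tie 0.28 to the meta-analyses, and the article does not give the comparators or standardisers behind their g values. The power figures at those values are therefore illustrative. Likewise, the power statement includes no allowance for dropout, but Table 1 leaves the target sample size blank, so the article does not establish that 100 is the recruitment ceiling. Neither point affects the conversion error.

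Finally, the correction changes no design feature and does not touch the type I error. That makes it cheap, but the trial is still credited with a sensitivity it lacks.

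**Conclusion.** The concern holds. The stated d is half the value implied by the protocol's own f. With 50 per group, two-sided alpha 0.05 and a correlation of 0.5, the trial has 80% power for a between-group difference in change of 0.566 single-time-point SDs, and 28% power at 0.28.

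The result rests on the protocol's inputs, on reading d as the difference in change that the hypothesis describes, and on standardising by the single-time-point SD (equal to the change-score SD when the correlation is 0.5).

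Two illustrations rest on assumptions that are not in the protocol. With a MoCA SD of 2.5 to 3.5 points, the detectable difference is about 1.4 to 2.0 points (0.566 × 2.5 and 0.566 × 3.5) rather than 0.7 to 1.0. With 10% or 20% loss (45 or 40 per group), the detectable d is 0.60 or 0.63.

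**What to change.** Keep N = 100 and f ≥ 0.14, and delete the d ≥ 0.28 equivalence. Suggested text: *f ≥ 0.14 for the group-by-time interaction, corresponding to a between-group difference in MoCA change of d ≥ 0.57, standardised by the SD at one time point and assuming a correlation of 0.5 between measurements.* If a baseline-adjusted ANCOVA is made the primary model, give d ≥ 0.49 instead.

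It would help to add that a non-significant result cannot exclude effects of the size cited in the Introduction. Any figure allowing for dropout should be labelled as an assumption.

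The cost is one or two sentences. Sample size, randomisation, endpoint and analysis are unchanged; the stated sensitivity becomes less favourable.
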